## Abstract

**Background:**

Shared decision-making improves the quality of patient care. Unfortunately, shared decision-making is not yet common practice among vascular surgeons. Thus, decision support tools were developed to assist vascular surgeons and their patients in using shared decision-making. This trial aims to evaluate the effectiveness and implementation of decision support tools to improve shared decision-making during vascular surgical consultations in which a treatment decision is to be made.

**Methods:**

The study design is a multicentre stepped-wedge cluster-randomised trial. Eligible patients are adult patients, visiting the outpatient clinic of a participating medical centre for whom several treatment options are feasible and who face a primary treatment decision for their abdominal aortic aneurysm, carotid artery disease, intermittent claudication, or varicose veins. Patients and vascular surgeons in the intervention group receive decision support tools that may help them adopt shared decision-making when making the final treatment decision. These decision support tools are decision aids, consultation cards, decision cards, and a practical training. Decision aids are informative websites that help patients become more aware of the pros and cons of the treatment options and their preferences regarding the treatment choice. Consultation cards with text or decision cards with images are used by vascular surgeons during consultation to determine which aspect of a treatment is most important to their patient. In the training vascular surgeons can practice shared decision-making with a patient actor, guided by a medical psychologist. This trial aims to include 502 vascular surgical patients to achieve a clinically relevant improvement in shared decision-making of 10 out of 100 points, using the 5-item OPTION instrument to score the audio-recordings of consultations.

**Discussion:**

In the OVIDIUS trial the available decision support tools for vascular surgical patients are implemented in clinical practice. We will evaluate whether these tools actually improve shared decision-making in the consultation room. The stepped-wedge cluster-randomised study design will ensure that at the end of the study all participating centres have implemented at least some of the decision support tools and thereby a certain level of shared decision-making.

**Trial registration:**

Netherlands Trial Registry, NTR6487. Registered 7 June 2017. URL: http://www.trialregister.nl/trialreg/admin/rctview.asp?TC=6487

## Background

Physicians aim to offer the best quality of care to their patients. In recent years it has been acknowledged that the incorporation of the patients’ preferences, known as shared decision-making (SDM), improves quality of care by enhancing patient satisfaction and therapy adherence [1, 2]. SDM also decreases the number of patients who opt for (major) invasive treatment or who undergo undesired care without adverse effects on health outcomes [1–5].

SDM may especially benefit patients in vascular surgery, because for many patients more than one treatment option is feasible, for example a conservative, endovascular or open surgical treatment, each with their own beneficial and potential harmful effects [6]. It is therefore essential that vascular surgeons are aware of how the patient weighs the benefits and harms of the available options. Unfortunately, studies show that in the Netherlands, the level of SDM is limited among vascular surgeons and that patients are informed inconsistently about their disease and treatment options [7, 8].

In order to improve SDM, a set of decision support tools (DSTs) has been developed for both vascular surgeons and patients. When developed and applied correctly, DSTs improve disease-specific knowledge and, more importantly, SDM in the consultation room [1, 5, 9–12].

DSTs have been developed for Abdominal Aortic Aneurysm (AAA), Carotid Artery Disease (CAD), Intermittent Claudication (IC) and Varicose Veins (VV). These DSTs are designed according to international standards [13] and consist of decision aids, consultation cards, decision cards, and a practical training in SDM for vascular surgeons, physician assistants, and nurse practitioners.

### Objectives

The objective of this trial is to evaluate the effectiveness and implementation of DSTs at the individual patient level to improve SDM during vascular surgical consultations in which a treatment decision is to be made for patients with an abdominal aortic aneurysm, carotid artery disease, intermittent claudication and varicose veins.

## Methods

The study protocol is designed according to the Standard Protocol Items: Recommendations for Interventional Trials (SPIRIT) statement and the CONsolidated Standards of Reporting Trials (CONSORT) extension for Cluster Trials [14, 15]**.** A filled out SPIRIT checklist regarding this trial is added as a supplementary file. The trial was registered in The Netherlands National Trial Registry as NTR6487, available at www.trialregister.nl.

### Trial design

The Operative Vascular Intervention Decision-making Improvement Using Sdm-tools (OVIDIUS) trial design is a 15-center stepped-wedge cluster randomised trial in the Netherlands, as shown in Table 1. Each cluster consists of three participating medical centres. The reasons for choosing this design is in the first place that it allows the evaluation of outcomes before and after introduction of the DSTs in the individual centres and limits the influence of any intercurrent changes in protocols on the clinical outcomes. Second, all participating centres will eventually have implemented at least some of the DSTs and thereby a certain level of SDM.

**Table 1 Tab1:**
[figure not shown]
Multicentre stepped-wedge cluster-randomised design

-: Before introduction of decision support tools

+: After introduction of decision support tools

: Introduction of decision support tools/evaluation moment

### Trial setting

Participating centres are located throughout the Netherlands and must provide care for at least one of the four vascular diseases for which the DSTs have been developed. The list of participating medical centres will be published alongside the trial results and is available upon request by emailing the corresponding author. Patients are to be included between January 1, 2018 and June 30, 2019.

### Eligibility criteria

Eligible patients are adults visiting the outpatient clinic of a participating centre who need to decide on a primary treatment for their AAA, CAS, IC or VV. These patients must be eligible for more than one treatment option. Table 2 shows a more detailed overview of the study’s inclusion and exclusion criteria.

**Table 2 Tab2:** Eligibility criteria

Inclusion criteria	Exclusion criteria
Age ≥ 18 years	Patients requiring emergency surgery
> 1 feasible treatment options	Life expectancy less than 1 year
(Newly) diagnosed with an asymptomatic AAA that has grown to ≥5 cm in women or ≥ 5.5 cm in men	ASA-IV patients
Newly diagnosed with symptomatic CAD with a > 70% stenosis within 6 months since the onset of symptoms, or > 50% in men diagnosed within 12 weeks since the onset of symptoms [16]	Insufficient understanding of the Dutch language
(Newly) diagnosed with invalidating IC (Fontaine II) Considering treatment for VV	Cognitively unable to complete Dutch questionnaires
Willing to sign an informed consent form	

### Interventions

The intervention comprises a set of DSTs, developed to help both vascular surgeons and patients to improve SDM. Use of the DSTs is compared to standard care at the level of individual participants. Standard care may include informative leaflets or websites that participating medical centres already provide to their patients.

The DSTs studied here are decision aids, consultation cards, decision cards and a practical training. The patient advocacy society (Heart and Vascular Group) and the Dutch professional society (Dutch Society for Vascular Surgery) provided intellectual support for the development of the DSTs. The Netherlands Organisation for Health Research and Development provided financial support (ZonMw, grant 516,022,506). The participating centres may decide which combination of DST they prefer to use.

*Decision aids* are validated web-based applications that provide patients with information about their disease and treatment options. In addition, it has an interactive section in which the patient is encouraged to consider what he or she believes is important when deciding on a treatment strategy [9, 17]. Patients receive the decision aid prior to the decision-making consultation via a personalised web link. The researchers automatically receive the answers given by patients in the decision aid regarding their disease-specific knowledge and treatment preferences. The following link provides access to the English version of the Dutch decision aid used in this study for patients with an AAA: https://sdmstaging.medify.eu/surgery1/index_da-aortic-aneurysm_en.html

More information about other available decision aids is provided at the website of the Ottawa Hospital Research Institute [18].

*Consultation cards* are validated tools, also known as Option Grids™ [19]. These are A4-sized paper sheets showing questions -with their answers- that patients most frequently ask about the treatment options, presented in a table format. Vascular surgeon and patient discuss the consultation cards during the consultation. The order in which the patient wants to discuss the questions provides insight into the aspects patients find relevant to them personally when deciding on a treatment strategy [11]. Table 3 shows the consultation card used in this study by vascular surgeons for patients with symptoms of intermittent claudication. More information about other available decision aids is provided at the website of the Dartmouth Institute [20].

**Table 3 Tab3:** Example of a consultation card for patients with intermittent claudication. Treatment options for intermittent claudication. Use this consultation card if you want to talk to your health care professional about how to treat your blocked or narrowed leg arteries (medical term: ‘intermittent claudication’). This way you can decide with your doctor which option is best for you

Frequently asked questions	(Supervised) exercise therapy	Endovascular treatment (with or without stenting)	Surgery (Endarterectomy or bypass)
What does the treatment entail?	You will exercise on a treadmill (supervised by a physical therapist) to increase your overall and pain-free walking distance. You also receive weight training exercises to practice at home.	A wire is inserted into the artery in your groin. Attached to this wire is a balloon. The balloon is inflated to reduce the narrowing. Sometimes, a tube is left behind to keep the artery open.	▪ With an ‘endarterectomy’ the artery is opened and the narrowing surgically removed. ▪ With a ‘bypass’ either one of your own veins or an artificial tube is used to bypass the narrowed artery.
	You will also continue to take medication to prevent a heart attack or stroke.	You will also continue to take medication to prevent a heart attack or stroke.	You will also continue to take medication to prevent a heart attack or stroke.
What are the benefits of this treatment?	Your general condition will improve due to exercise therapy. There are no treatment risks.	Your complaints will be less immediately after endovascular treatment.	Your complaints will be less immediately after surgery.
What are the main risks associated with the treatment?	You will not have an immediate effect of exercise therapy. It takes about 3 to 6 months before you experience improvement. Some patients will not be able to walk completely pain-free after exercise therapy.	You may suffer from a hematoma (bruise), a reduced kidney function, or the endovascular treatment might even worsen your complaints.	You may suffer from a hematoma (bruise), a wound infection, or the surgery might even worsen your complaints.
What is the effect of the treatment?	After 6 months of exercise therapy, patients like yourself are able to walk twice as far as before the exercise therapy.	Two years after endovascular treatment, the walking distance is about the same as after exercise therapy only.	Two years after surgery, the walking distance is about the same as after exercise therapy only.
Will I receive anaesthesia?	No.	Yes; local anaesthesia.	Yes; general or local anaesthesia.
How long do I stay in the hospital?	No hospital stay.	Usually 1 to 2 days.	Usually 1 week.
What is the risk of losing my leg (amputation)?	1 to 3 of 100 people (1–3%) with intermittent claudication have an amputation within 10 years.	1 to 3 of 100 people (1–3%) with intermittent claudication have an amputation within 10 years.	1 to 3 of 100 people (1–3%) with intermittent claudication have an amputation within 10 years.
What more should I need to know about intermittent claudication?	Exercise therapy does not prevent worsening of the disease. In case of insufficient results, endovascular treatment and surgery are still possible.	Endovascular treatment does not prevent worsening of the disease. Even if you have undergone this treatment, exercise therapy will remain helpful.	Surgery does not prevent worsening of the disease. Even if you have undergone surgery, exercise therapy will remain helpful.
What can I do myself?	The most important things you can do to prevent worsening of the disease is to quit smoking, take plenty of exercise, healthy food, and live a healthy life.	The most important things you can do to prevent worsening of the disease is to quit smoking, take plenty of exercise, healthy food, and live a healthy life.	The most important things you can do to prevent worsening of the disease is to quit smoking, take plenty of exercise, healthy food, and live a healthy life.

Authors: Department of Vascular Surgery Amsterdam UMC location AMC, Heart and Vascular Group, Dutch Society for Vascular Surgery

Based on: most recently available literature

Publication date: May 16, 2017

*Decision cards* are tools designed with the same purpose as consultation cards. Here each question with its answer is presented on a different card. The answers are provided in the form of images, which is supposed to have a beneficial effect on doctor-patient interaction as it leaves room for tailor-made information based on patient comorbidity or hospital performance [10]. Fig. 1 shows the decision cards addressing symptomatic carotid artery disease used in this study by vascular surgeons with their patients. More information about how to use decision cards is provided at the website of the Mayo Clinic Shared Decision Making National Resource Center [21].

**Fig. 1 Fig1:**
[figure not shown]
Carotid artery disease decision cards

*The practical training* is offered to all vascular surgeons, physician assistants and nurse practitioners in the participating centres. The training allows participants to practice the three important steps of SDM, which are the ‘team talk’, ‘option talk’ and ‘decision talk’ [22]. The participants practice these steps with a patient actor under the guidance of a medical psychologist [12, 22]. The practical training takes place just before the vascular surgeons start using the DSTs in their centre.

### Outcomes

The primary outcome is the level of SDM during the consultation as scored with the 5-item Observing patient involvement (OPTION) instrument [23]. The 5-item OPTION instrument allows researchers to objectively assess the level of patient involvement in the decision-making process as scored from audio-recordings of the consultations [24]. If the vascular surgeon and patient need more than one consultation to reach a treatment decision, all consultations are audio-recorded and scored as one consultation. Afterwards, two researchers independently score the five OPTION-items on a five-point scale. The cumulative OPTION-score is expressed on a 100-point scale.

Baseline characteristics, i.e. age, gender, diagnosis, highest level of education, employment status, social status, and ethnicity, are collected from the patients using a questionnaire before consultation.

Secondary outcomes are patients’ disease specific knowledge, decisional conflict, quality of life, and SDM as perceived by patients, SDM as perceived by vascular surgeons, the treatment decided upon, the implementation of DSTs, and process measures.

The patients’ disease-specific knowledge is scored directly after the consultation. The questions test whether patients correctly understood the information presented in the decision aid or received during the consultation.

Decisional conflict in patients is scored directly after the consultation and is repeated 4 weeks after consultation in which the treatment decision is made [17]. If an endovascular or open surgical treatment takes place within 4 weeks, decisional conflict is scored just before treatment. The decisional conflict in patients is scored using the 16-item Decisional Conflict Scale (DCS) [25].

Quality of life in patients is scored directly after consultation and again 6 weeks after treatment with the Short Form Health Survey (SF12) [26].

SDM as perceived by patients is scored directly after consultation using the SDM-Q-9 questionnaire, the 3-item CollaboRATE questionnaire, and the one-question Control Preference Scale and Control Perception Scale (CPS) [27–29]. The Control Preference Scale documents the desired amount of patient involvement and is scored before the consultation. The Control Perception Scale assesses the actually perceived amount of patient involvement and is scored after the consultation.

SDM as perceived by vascular surgeons is scored after the consultation using the SDM-Q-DOC questionnaire and the Control Perception Scale [29, 30].

The treatment decided upon is derived from the audio recording of the consultation. The actually received treatment is obtained from the participating vascular surgeon or centre.

The extent in which DSTs are implemented is determined by scoring the number of times a specific tool is used as recorded by the audio recording (consultation card and decision cards). Successful use of the decision aid is defined as completion of the decision aid by the patient. Completion and time to complete is recorded automatically when patients access the decision aid via the provided link.

Process measures studied are the number and duration of consultations necessary to decide upon a treatment, as obtained from the audio recording(s) or from the participating vascular surgeon or centre.

All outcomes mentioned above are evaluated at the individual participant level.

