### Participants’ timeline

Figure 2 provides an overview of the participants’ timeline. Patients in the intervention group receive the decision aid prior to the appointment at the outpatient clinic. Patient follow-up is finalised after the patient has completed the final questionnaire. Patients receive the final questionnaire 6 weeks after the treatment or, in case of conservative treatment, 6 weeks after the decision-making consultation.

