### Statistical methods

Baseline characteristics are summarised using descriptive statistics. Unevenly distributed outcome measures are expressed as medians and inter-quartile ranges. A differential effect among the four included vascular diseases is not expected, as the primary outcome is SDM. SDM is equally applicable to each of these diseases since multiple treatment options are available. Nevertheless, the sample size is sufficient to analyse the effect on SDM for each disease separately.

Differences in mean scores of the 5-item OPTION instrument between consultations in which usual care is provided (control group) and the consultations in which DSTs are used (intervention group), are analysed using the Student t-test with Satterthwaite correction for unequal variances. ANCOVA is applied to correct for possible baseline differences in patients before and after the introduction of the DSTs.

Differences in (semi-)continuous variables between the usual care group and the DSTs group (e.g. Likert scales and quality of life scores) are analysed by means of the Student t-test or the non-parametric Mann-Whitney U test, depending on the normality of their distribution. Percentages are compared using a Chi-square test (e.g. for the final treatment choice). In particular, before-after differences in DCS at 4 weeks are analysed after correcting for differences between the groups in baseline DCS. Logistic regression analysis is used to determine the individual effect of the different DSTs on our primary outcome. Statistical analyses will be conducted using IBM SPSS version 24 (IBM, Armonk, NY, USA).

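### The first SF-12 is taken after exposure to the decision support tools, and quality of life is compared by tests that take no covariate

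*Protocol article*

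**What the plan says.** All places are in the protocol article.

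- **Timing.** Outcomes schedules SF-12 twice: "Quality of life in patients is scored directly after consultation and again 6 weeks after treatment". Participants' timeline sets the final questionnaire for patients treated without an intervention at this point: "in case of conservative treatment, 6 weeks after the decision-making consultation". The text describes no SF-12 before the consultation.
- **Exposure.** Participants' timeline: "Patients in the intervention group receive the decision aid prior to the appointment at the outpatient clinic". Under Interventions, the cards are used within the consultation itself.
- **Analysis.** Statistical methods: "quality of life scores) are analysed by means of the Student t-test or the non-parametric Mann-Whitney U test, depending on the normality of their distribution". The one secondary score with a stated correction for an earlier value is the decisional conflict scale: "before-after differences in DCS at 4 weeks are analysed after correcting for differences between the groups in baseline DCS". The ANCOVA sentence stands in the paragraph on the OPTION score.
- **Existing form.** Outcomes says that age, gender, diagnosis and four other characteristics "are collected from the patients using a questionnaire before consultation". The Control Preference Scale is also taken before the consultation.

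**The concern.** A baseline serves two purposes: it shows whether the groups were alike before exposure, and it removes between-patient variance from the follow-up comparison. As written, SF-12 is not set up for the first purpose, and the named tests do not serve the second.

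Imbalance is plausible in this design. Patients are approached one by one as they attend (Recruitment), when their cluster's status is already settled (Allocations), and neither patients nor surgeons are blinded (Blinding). The Discussion concedes a possible inclusion bias. It also says that the four diseases differ in incidence and that the researchers will act if one is included much more often than another. Disease mix may therefore drift over calendar time, and in a stepped wedge the share of exposed patients rises with calendar time. If health status differs by disease, such a drift would appear in an unadjusted two-group test as a difference in quality of life.

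This is more than detail left to an analysis plan. The article states both the timing and the test, and a later plan could add covariates but not a pre-exposure score that was never collected.

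**Working it through.** **Figures in the plan.** None is given for SF-12. The sample size rests on OPTION: 58 × 1.944 = 112.8, taken as 113 per disorder; 113 × 4 = 452; 452 / 0.9 = 502.2, stated as 502. Nothing in this chain uses SF-12, so the point does not touch it.

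**Sequence for an intervention patient.** Decision aid, then consultation with cards, then first SF-12, then treatment where one is given, then second SF-12. The first score precedes treatment but follows exposure to the tools.

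**Gain from adjustment.** Let r be the within-group correlation between the earlier and the 6-week score. The documents do not give it; 0.3 to 0.7 is assumed. Adjusting for the earlier score multiplies the patient-level residual variance by 1 − r², and the interval width by √(1 − r²).

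| r | 1 − r² | Variance reduction | Width factor | Interval narrower by |
|---|---|---|---|---|
| 0.3 | 0.91 | 9% | 0.954 | 5% |
| 0.5 | 0.75 | 25% | 0.866 | 13% |
| 0.6 | 0.64 | 36% | 0.800 | 20% |
| 0.7 | 0.51 | 49% | 0.714 | 29% |

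**If the tested variable were a change score.** With equal SDs at both times, a t-test on change has variance factor 2(1 − r): 1.40 at r = 0.3, 1.00 at 0.5 and 0.60 at 0.7. The adjusted model has 0.91, 0.75 and 0.51. The ratio is (1 + r)/2, that is 0.65, 0.75 and 0.85, so adjustment is better throughout this range.

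**What the timing adds.** The adjusted contrast is the follow-up difference minus b times the difference in the earlier score, with b = r when the SDs are equal. If the tools themselves move the first SF-12, a fraction r of that movement (30% to 70% here) is subtracted from the follow-up difference. With a pre-exposure score, the same subtraction removes only prior imbalance. The documents give nothing from which to judge how large an immediate effect on SF-12 might be.

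**The case against.** **The loss of precision is not due to the timing.** This stands. The post-consultation score precedes treatment and, used as a covariate, could recover much of the variance. The named tests cause the loss; the timing decides only whether the adjustment is clean. A tool that informs a choice also has a more direct route to knowledge or decisional conflict than to general health, so the contamination may be small.

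**The plan might use the first score after all.** This stands in part. Statistical methods does not say whether the tested variable is the first score, the 6-week score or the change. A reader might infer that the first SF-12 is never used, but the text does not exclude a change score. One might also extend the ANCOVA sentence to every outcome. Even so, no pre-exposure SF-12 would exist to adjust for, and a change score is less precise than the adjusted model.

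**A true baseline is not free.** This stands. A reader might infer that the existing form already gives a pre-exposure slot. Outcomes places the form before the consultation, not before the decision-aid link, which is also sent ahead of the appointment. The timeline figure is not shown.

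**The size is illustrative.** This stands. Treatment falls between the two scores for many patients, and the interval between them varies, so r may be low. It would also be wrong to turn the gain into an equivalent number of patients: that would ignore clustering and borrow a total that was sized for OPTION.

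**Conclusion.** The point holds as an improvement to one secondary outcome. The first SF-12 follows exposure to the tools, and the stated comparison of quality of life takes no covariate, in a trial that pools four diseases and recruits without blinding after allocation.

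The direction of the precision gain is certain if r is above zero. Its size, about 9% to 49% less residual variance and intervals about 5% to 29% narrower, rests wholly on the assumed correlation of 0.3 to 0.7 and concerns patient-level variance. Most of that gain is open to the trial even with the present timing; moving the first SF-12 mainly buys a baseline that the tools cannot have altered. Adjustment for the earlier score would not by itself deal with clustering or calendar time, which the two named tests also ignore.

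**What to change.** 1. **Statistical methods.** Replace the two-group test for SF-12 with a regression of each 6-week component score on the earlier SF-12 score and diagnosis (already collected), with centre or cluster terms and period terms. The model must be written out, because the article defines none for the secondary continuous outcomes.
2. **Outcomes.** Move the first SF-12 to the pre-consultation questionnaire and require that it be completed before the decision-aid link is released.
3. **Patients already recruited.** Adjust for the post-consultation score, and state that any immediate effect of the tools would be partly adjusted away. If both timings occur, let the coefficient of the earlier score differ between them, since the change of timing will coincide with calendar time.

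The cost is twelve items moved to the first form, which becomes longer, a sequencing requirement relative to the link, a few sentences of text and possibly two timings in the data. No extra patients are needed.
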